### Statistical Analysis and Number of patients needed

The trial is designed on the basis of a critical review of the existing evident data on steroid- resistant acute rejection in liver transplantation and the use of de novo CNI-free immunosuppressive regimens. Steroid resistant acute rejection is the interesting parameter for the planned intervention since this is a threat for irreversible acute rejection and organ loss. A prospective uncontrolled two-step design was chosen for several reasons: there are hardly data on a de novo CNI-free immunosuppressive regimen. Therefore, we intended to design an uncontrolled pilot-trial, which is feasible for a single center, but is represented by a reasonable end-point. The two-step design offers this possibility with the inclusion of a first group of 9 patients, a consecutive evaluation and decision if the trial has to be terminated prematurely or if in the second step the hypothesis can be further confirmed by including additional 20 patients aiming at 29 patients in total [19]. This is a prospective, open-label, two-stage study. The primary endpoint is the incidence of steroid resistant acute rejection within the first 30 days after liver transplantation (LT). Based on Cochrane database and Medline database data including a total of 2.200 patients, the incidence of steroid resistant rejection within the first year after transplantation with the commonly used CNI-based and CNI-reduced protocols is 12.5% of all patients undergoing LT. This means that 87.5% of patients are without steroid resistant rejection (i.e., the response proportion is 87.5%). Based on this estimation a two-stage design [19] will be applied to test the following statistical hypothesis: *H_0_*: The true response probability *p *is less than the uninteresting level *p_0_*(*p *≤ *p_0_*). Versus *H_1_*: The true response probability *p *is at least the target level *p_1_*(*p *≥ *p_1_*). In this study, the uninteresting level will be defined as *p_0_*= 0.80, which means that 20% of our examined cohort would experience a steroid resistant early acute rejection within the first 30 days after LT. The target level will be defined as *p_1_*= 0.95, which means that 5% of our collective would experience a steroid resistant early rejection within the first 30 days. Under these assumptions, 9 patients will be enrolled in the first stage. After testing the immunosuppressive regimen on 9 patients in the first stage, the trial will be terminated if 7 or fewer respond to the therapy. If the trial goes to the second stage, an additional 20 patients will be enrolled. With a total of 29 patients, the following decisions will be made: If 26 or fewer responders are observed then H_0 _cannot be rejected. In this case, the immunosuppressive therapy is not promising with a high probability and is not worth to be tested in a greater trial for this indication. If 27 or more responders are observed, then H_0 _can be rejected. In this case, the immunosuppressive regimen is considered promising. If the therapy is actually not promising, there is a 0.049 probability of concluding that it is (the target significance level was set to 5%). If the therapy is actually promising, there is a 0.198 probability of concluding that it is not (the target for this value was set to 20%). The confirmatory analysis will be performed for the intent-to-treat population. Figure 2 shows a statistical flowchart for the trial.

**Figure 2 F2:**
[figure not shown]
**Statistical flow-chart**. The flow chart shows the two-step model of the single-arm prospective trial. If there are more than 8 responders (patients that do not have steroid-resistant acute rejection within 30 days after transplantation.) after inclusion of 9 patients, there will be a second stepp with additional inclusion of 20 patients. If more than 27 patients do not show steroid resistant acute rejection, the proposed treatment regimen is promising.

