**Methods/Design:**

Patients older than 18 years with renal impairment at the time of liver transplantation eGFR < 50 ml/min and/or serum creatinine levels > 1.5 mg/dL will be included. Patients in will receive a CNI-free combination therapy (basiliximab, MMF, steroids and delayed Sirolimus). Primary endpoint is the incidence of steroid resistant acute rejection within the first 30 days after LT. The study is designed as prospective two-step trial requiring a maximum of 29 patients. In the first step, 9 patients will be included. If 8 or more patients show no signs of biopsy proven steroid resistant rejection, additional 20 patients will be included. If in the second step a total of 27 or more patients reach the primary endpoint the regimen is regarded to be safe and efficient.

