### Current status

**PATRON07 **started to actively recruit in December 2008 and currently has 9 patients included, which indicates the first interim analysis. Data are currently cleaned and evaluated.

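### The Figure 2 legend sets both decision cut-offs one responder higher than the statistical section; followed literally, it gives about 46% power, not the stated 80%

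*Protocol article*

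**What the plan says.** **Statistical section** (Statistical Analysis and Number of patients needed). After nine patients, "the trial will be terminated if 7 or fewer respond to the therapy", so stage 2 opens at 8 or 9. With 29 patients, H0 stands at 26 or fewer responders. "If 27 or more responders are observed", H0 is rejected. The stated error probabilities are 0.049 (type I) and 0.198 (type II).

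**Abstract** (Methods/Design). The cut-offs are the same, 8 or more and then 27 or more, but success is worded as follows: "a total of 27 or more patients reach the primary endpoint the regimen is regarded to be safe and efficient". Elsewhere the primary endpoint is defined as the incidence of steroid-resistant rejection, which is the adverse event.

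**Figure 2 legend.** Stage 2 follows "If there are more than 8 responders" among the first nine. For the final decision: "If more than 27 patients do not show steroid resistant acute rejection, the proposed treatment regimen is promising".

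**Current status.** The trial "currently has 9 patients included, which indicates the first interim analysis".

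**The concern.** Both cut-offs in the legend sit one responder above those in the statistical section, and that section refers the reader to Figure 2 as the trial's statistical flow-chart. The two rules disagree at two outcomes:

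- Exactly 8 of 9 at stage 1: the statistical section continues; the legend does not open stage 2.
- Exactly 27 of 29 at the end: the statistical section rejects H0; the legend does not call the regimen promising.

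This is the trial's only confirmatory decision. The stage 1 data were being evaluated when the article was written, so a single steroid-resistant rejection among the first nine patients would put the trial exactly where the rules part. Two published rules also leave room to choose between them after the data are seen, which would void the stated error rates.

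**Working it through.** **Inputs, all from the statistical section unless noted**

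- p0 = 0.80: "which means that 20% of our examined cohort would experience a steroid resistant early acute rejection within the first 30 days after LT".
- p1 = 0.95: "which means that 5% of our collective would experience a steroid resistant early rejection within the first 30 days".
- Stage 1 has 9 patients and stage 2 has 20, for a total of 29.
- Statistical section rule: continue if X1 ≥ 8, succeed if X1 + X2 ≥ 27.
- Legend rule (Figure 2): continue if X1 = 9, succeed if X1 + X2 ≥ 28.

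**Formula**

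With X1 ~ Bin(9, p) and X2 ~ Bin(20, p), stage 1 cut-off a1 and final cut-off a:

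P(success) = Σ over x = a1,…,9 of P(X1 = x) × P(X2 ≥ a − x).

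**Components**

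| | p = 0.80 | p = 0.95 |
|---|---|---|
| P(X1 = 9) = p^9 | 0.1342 | 0.6302 |
| P(X1 = 8) = 9 p^8 (1 − p) | 0.3020 | 0.2985 |
| P(X2 ≥ 18) | 0.2061 | 0.9245 |
| P(X2 ≥ 19) | 0.0692 | 0.7358 |
| P(X2 = 20) | 0.0115 | 0.3585 |

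**Step 1: reproduce the plan's figures with the statistical section rule**

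Nine responders in stage 1 need 18 more; eight need 19 more.

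- Type I error: 0.1342 × 0.2061 + 0.3020 × 0.0692 = 0.0277 + 0.0209 = 0.0486 (stated 0.049).
- Power: 0.6302 × 0.9245 + 0.2985 × 0.7358 = 0.5827 + 0.2197 = 0.8024. The type II error is 1 − 0.8024 = 0.1976 (stated 0.198).

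Both match. A search over two-stage designs with a total size from 15 to 39 also returns these cut-offs (7 of 9, 26 of 29) as the Simon optimal design for p0, p1 and the 5% and 20% targets.

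**Step 2: apply the legend rule**

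All nine must respond in stage 1, and then at least 19 of 20.

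- Type I error: 0.1342 × 0.0692 = 0.0093.
- Power: 0.6302 × 0.7358 = 0.4638.

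**Step 3: take only one of the legend's cut-offs**

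- 9 of 9, then 27 or more: type I error 0.1342 × 0.2061 = 0.0277; power 0.6302 × 0.9245 = 0.583.
- 8 or more of 9, then 28 or more: type I error 0.0093 + 0.3020 × 0.0115 = 0.0128; power 0.4638 + 0.2985 × 0.3585 = 0.571.

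No combination that uses a legend cut-off gives the stated error rates.

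**Step 4: how often the rules disagree**

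- Not passing stage 1 at p = 0.95: 1 − 0.6302 − 0.2985 = 0.071 (statistical section) against 1 − 0.6302 = 0.370 (legend).
- Exactly 8 of 9: 0.299 at p = 0.95 and 0.302 at p = 0.80.
- Stage 2 opened under the statistical section rule and exactly 27 of 29 at the end, p = 0.95: 0.8024 − 0.5708 = 0.232.
- Opposite overall conclusions at p = 0.95: every success under the legend is also a success under the statistical section, so the probability is 0.8024 − 0.4638 = 0.339.

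**The case against.** The strongest reply is that nothing in the design is wrong. The statistical section gives both sides of the final boundary and the matching error rates, the abstract repeats the cut-offs, and the figures reproduce. A reader can therefore recover the intended rule. The legend looks like a slip, with more than written for at least, twice. The 46% arises only if someone follows the legend and ignores the rest.

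That is correct as far as it goes: the power of the rule in the statistical section remains 80%, and 46% describes the legend's rule only. It explains the mismatch without removing it, because a flow-chart is a natural place to look when a go/no-go decision is made.

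Three narrower points also stand:

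- The drawing itself was not available, so the finding rests on the legend; the boxes may carry the right numbers.
- The legend says when stage 2 opens and has no explicit stopping statement. Stopping at 8 of 9 is what it implies. The article does not say which wording is being used for the interim decision.
- The abstract's wording about reaching the endpoint is minor. The sentence before it speaks of patients without resistant rejection, so the intent is clear.

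**Conclusion.** The concern holds. The article gives two incompatible versions of its only confirmatory decision rule, and its own error rates show that the legend is the version in error. Followed literally, the legend lowers power at p = 0.95 from 0.802 to 0.464 and the type I error at p = 0.80 from 0.0486 to 0.0093. It would also make a truly promising regimen about five times as likely not to pass stage 1 (0.370 / 0.071 = 5.2).

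The figures rest on the article's p0 and p1, independent patients with a common response probability, all 29 evaluable under intention to treat, and a literal reading of more than. The correction must be made because it concerns a decision threshold that is about to be used. The reversed wording in the abstract is a secondary, editorial point.

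**What to change.** 1. In the Figure 2 legend, state 8 or more responders of 9 for opening stage 2 and 27 or more of 29 for calling the regimen promising. Check that the boxes in the drawing agree.
2. In the abstract, describe success as 27 or more patients free of steroid-resistant rejection at day 30, in place of patients reaching the primary endpoint.
3. Record, for the trial team and the data safety monitoring board, that the rule in the statistical section governs the current interim decision. Do this before the stage 1 result is acted on.

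The cost is a correction to a legend and one sentence of the abstract, plus a short file note. Sample size, hypotheses and stated error rates do not change.

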### Trial organization, quality control and registration

The study was designed at Regensburg University Medical Center, Department of Surgery in cooperation with the Regensburg University Medical Center, Center for Clinical Studies. Quality assurance will be carried out in cooperation with the Clinical Transplantation Study Group of the Regensburg University Medical Center, Department of Surgery. The studies will be monitored by an independent monitor of the Clinical Transplantation Study Group. The studies will be performed in accordance with the Declaration of Helsinki in its current German version and the Good Clinical Practice/International Committee of Harmonization-guidelines (GCP/ICH). The study has been approved by the independent Regensburg University Ethical Review Board on November 16^th ^2007. Final approval for the trial by the BfArM has been obtained in November 2008 (EudraCT number 2007-003561-40). The start of the study was registered at the particular authority (Regierungsoberbehörde der Oberpfalz in Regensburg) on January 15^th ^2008. Additionally, it was registered under http://www.clinicaltrials.gov on January 15^th ^2008 (NCT00604357).

### Current status

**PATRON07 **started to actively recruit in December 2008 and currently has 9 patients included, which indicates the first interim analysis. Data are currently cleaned and evaluated.

## Discussion

The **PATRON07**-study to establish CNI-free-"bottom-up" strategies in LT recipients with renal impairment prior to LT aims at minimizing IS in a "bottom-up" approach in contrast to classical "top-down" strategies aiming at improvement of renal impairment and infectious complications in a specific group of highly ill liver allograft recipients. **PATRON07 **is a prospective, non-controlled, two-stage study. Its objective is to evaluate the feasibility of a de novo CNI-free immunosuppressive regimen based on induction therapy with anti-CD25 monoclonal anti- body, mycophenolate mofetil (MMF/MPA), and mTOR-inhibition with sirolimus in patients with impaired renal function at the time of liver transplantation. The primary endpoint is defined as the incidence of steroid-resistant acute rejection within the first 30 days after liver transplantation. It reflects the early potential and feasibility of the proposed immunosuppressive regimen with regards to safety and efficacy. In a liver transplant setting an acute rejection can be controlled with steroid treatment and does not necessarily mean an irreversible damage to the liver. Therefore, classical endpoints in liver transplantation like renal outcome measures or graft and patient survival will be of interest once the completely new approach of bottom-up immunosuppression has been established.

Former studies evaluated the effect of the reversibility of CNI toxicity by introducing reduced or delayed CNI based regimens or by switching patients to other substances like mTOR-inhibitors or MMF in a "top-down"-fashion. Our intention with a de novo CNI free-"bottom-up" IS strategies is to generally avoid CNI toxicity in patients that already have impaired renal function a priori.

The study concept is designed as sequential concept performing 2 separate independent clinical trials. **PATRON07 **has to be performed as a first step since there is hardly published evidence for CNI-free de novo approaches with mTOR-inhibitors in LT collectives. The trial is designed as a prospective, uncontrolled, two-step design according to Simon [19]. This is a major advantage with regard to costs and feasibility of the trial. We intend to prove the safety and efficacy of a therapy regimen that has not been introduced in a prospective clinical setting in liver transplantation. Therefore, we first need safe and effective preliminary data from this pilot study to be able to offer it to a broader collective of patients in a prospective randomized trial focusing on a different renal-specific endpoint. With this design we found a suitable way to address a specific scientific clinical problem in a prospective setting, which is feasible for one single center without funding by a large pharmaceutical-company.

## Conclusion

We conclude, that if CNI-free-"bottom-up" IS strategies are safe and effective, this may be an innovative concept that could improve the patient short and long-time outcome with regards to renal function, infectious complications and avoidance of over-immunosuppression after LT. The results of **PATRON07 **may be the basis for a large multicenter RCT in patients with poor renal function at the time-point of LT.
